**17. G6PD result:** ☐☐.☐ **IU/g Hb**

18. **Schizontocidal Treatment**

| Schizontocidal treatment | Pf | Pv | mixed |
| --- | --- | --- | --- |
| 1^st^ Dose (observed) | AL given  ☐ Yes ☐ No ☐  Dose:___________ | CQ given  ☐ Yes ☐ No ☐  Dose:___________ | AL given  ☐ Yes ☐ No ☐  Dose:___________ |
| 2^nd^ Dose | AL given  ☐ Yes ☐ No ☐  Dose:___________ | N/A | AL given  ☐ Yes ☐ No ☐  Dose:___________ |
|  | Was this dose given as observed treatment  ☐yes ☐no |  | Was this dose given as observed treatment  ☐yes ☐no |

19. **Primaquine treatment**

| Primaquine treatment | Pf | Pv | mixed |
| --- | --- | --- | --- |
|  | PQ single dose provided tp patient  ☐ Yes ☐ No ☐  Dose:___________ | PQ full course provided to patient  ☐ Yes ☐ No ☐  Dose:___________ | PQ full course provided to patient  ☐ Yes ☐ No ☐  Dose:___________ |

**Day – 6: Date of visit:** ☐☐-☐☐-☐☐☐☐

20. **Temperature:** ☐☐.☐˚C

21. **Finger prick collected?** ☐ Yes ☐ No

*If yes:* **Blood slide collected?** ☐ Yes ☐ No

*If yes:* Time: ☐☐:☐☐ in 24:00 format (e.g. 4pm is 16:00)

**Parasite count** ________/500RBC or ___________/200WBC

Diagnosis: ☐ Pf ☐ Pv ☐Mixed ☐neg

*If yes:* **Hemoglobin measured?** ☐ Yes ☐ No

*if Yes:* ☐☐.☐ g/dl

**Day – 9: Date of visit:** ☐☐-☐☐-☐☐☐☐

22. **Temperature:** ☐☐.☐˚C

23. **Finger prick collected?** ☐ Yes ☐ No

*If yes:* **Blood slide collected?** ☐ Yes ☐ No

*If yes:* Time: ☐☐:☐☐ in 24:00 format (e.g. 4pm is 16:00)

**Parasite count:** ________/500RBC or ___________/200WBC

Diagnosis: ☐ Pf ☐ Pv ☐Mixed ☐neg

*If yes:* **Hemoglobin measured?** ☐ Yes ☐ No

*if Yes:* ☐☐.☐ g/dl

**Day – 12: Date of visit:** ☐☐-☐☐-☐☐☐☐

24. **Temperature:** ☐☐.☐˚C

25. **Finger prick collected?** ☐ Yes ☐ No

*If yes:* **Blood slide collected?** ☐ Yes ☐ No

*If yes:* Time: ☐☐:☐☐ in 24:00 format (e.g. 4pm is 16:00)

**Parasite count :** ________/500RBC or ___________/200WBC

Diagnosis: ☐ Pf ☐ Pv ☐Mixed ☐neg

*If yes:* **Hemoglobin measured?** ☐ Yes ☐ No

*if Yes:* ☐☐.☐ g/dl

**Day – 16: Date of visit:** ☐☐-☐☐-☐☐☐☐

26. **Temperature:** ☐☐.☐˚C

27. **Finger prick collected?** ☐ Yes ☐ No

*If yes:* **Blood slide collected?** ☐ Yes ☐ No

*If yes:* Time: ☐☐:☐☐ in 24:00 format (e.g. 4pm is 16:00)

**Parasite count :** ________/500RBC or ___________/200WBC

Diagnosis: ☐ Pf ☐ Pv ☐Mixed ☐neg

*If yes:* **Hemoglobin measured?** ☐ Yes ☐ No

*if Yes:* ☐☐.☐ g/dl

28. **Meth hemoglobin measured (only Pf/Pv and Pv patients > 2 years)?** ☐ Yes ☐ No

*if Yes:* ☐☐.☐ in %

29. **# of days PQ tablets taken:** ___________________________________________

30**. Remaining tablets:** _____________________________________________ ☐Don’t known

**Day – 23: Date of visit:** ☐☐-☐☐-☐☐☐☐

24. **Temperature:** ☐☐.☐˚C

25. **Finger prick collected?** ☐ Yes ☐ No

*If yes:* **Blood slide collected?** ☐ Yes ☐ No

*If yes:* Time: ☐☐:☐☐ in 24:00 format (e.g. 4pm is 16:00)

**Parasite count :** ________/500RBC or ___________/200WBC

Diagnosis: ☐ Pf ☐ Pv ☐Mixed ☐neg

*If yes:* **Hemoglobin measured?** ☐ Yes ☐ No

*if Yes:* ☐☐.☐ g/dl

**Day – 30: Date of visit:** ☐☐-☐☐-☐☐☐☐

24. **Temperature:** ☐☐.☐˚C

25. **Finger prick collected?** ☐ Yes ☐ No

*If yes:* **Blood slide collected?** ☐ Yes ☐ No

*If yes:* Time: ☐☐:☐☐ in 24:00 format (e.g. 4pm is 16:00)

**Parasite count :** ________/500RBC or ___________/200WBC

Diagnosis: ☐ Pf ☐ Pv ☐Mixed ☐neg

*If yes:* **Hemoglobin measured?** ☐ Yes ☐ No

*if Yes:* ☐☐.☐ g/dl

**1^st^ Unscheduled visit: Date of visit:** ☐☐-☐☐-☐☐☐☐

31. **Temperature:** ☐☐.☐˚C

32. **Finger prick collected?** ☐ Yes ☐ No

*If yes:* **Blood slide collected?** ☐ Yes ☐ No

*If yes:* Time: ☐☐:☐☐ in 24:00 format (e.g. 4pm is 16:00)

**Parasite count :** ________/500RBC or ___________/200WBC

Diagnosis: ☐ Pf ☐ Pv ☐Mixed ☐neg

*If yes:* **Hemoglobin measured?** ☐ Yes ☐ No

*if Yes:* ☐☐.☐ g/dl

33. **Meth hemoglobin measured (only Pf/Pv and Pv patients > 2 years)?** ☐ Yes ☐ No

*if Yes:* ☐☐.☐ in %

**2^nd^ Unscheduled visit: Date of visit:** ☐☐-☐☐-☐☐☐☐

34. **Temperature:** ☐☐.☐˚C

35. **Finger prick collected?** ☐ Yes ☐ No

*If yes:* **Blood slide collected?** ☐ Yes ☐ No

*If yes:* Time: ☐☐:☐☐ in 24:00 format (e.g. 4pm is 16:00)

**Parasite count :** ________/500RBC or ___________/200WBC

Diagnosis: ☐ Pf ☐ Pv ☐Mixed ☐neg

*If yes:* **Hemoglobin measured?** ☐ Yes ☐ No

*if Yes:* ☐☐.☐ g/dl

36. **Meth hemoglobin measured (only Pf/Pv and Pv patients > 2 years)?** ☐ Yes ☐ No

*if Yes:* ☐☐.☐ in %

**SYMPTOM REPORTING FORM - Page 1**

| **Type of AE**  **(one per row only)** | **Onset Date** | **Severity Grade**  **(check one)** | **Actions Taken?**  **(specify below if needed)** | **Is AE related to PQ?**  **(check one)** | **Date Resolved** | **Outcome of AE (check one)** |
| --- | --- | --- | --- | --- | --- | --- |
| ☐Rash  ☐Nausea  ☐Vomiting  ☐Abdominal pain  ☐Dark Urine  Hillmen index: _ _  ☐Diarrhea  ☐Poor appetite  ☐Other (describe): _________________ | _ _ / _ _ / _ _ | ☐ Mild  ☐ Moderate  ☐Severe  ☐ Life-threatening | ☐ None  ☐ Stopped PQ  ☐ Prescribed drug  ☐ Blood Transfusion  ☐ Hospitalization  ☐ Other** | ☐ Unrelated  ☐ Unlikely  ☐ Possible  ☐ Probable  ☐ Definite | _ _ / _ _ / _ _  or ongoing ☐ | ☐ Recovered/resolved  ☐ Recovered/resolved with sequelae  ☐ Recovering/resolving  ☐ Not recovered/not resolved  ☐ Fatal  ☐ Unknown |
| ☐Rash  ☐Nausea  ☐Vomiting  ☐Abdominal pain  ☐Dark Urine  Hillmen index: _ _  ☐Diarrhea  ☐Poor appetite  ☐Other (describe): _________________ | _ _ / _ _ / _ _ | ☐ Mild  ☐ Moderate  ☐Severe  ☐ Life-threatening | ☐ None  ☐ Stopped PQ  ☐ Prescribed drug  ☐ Blood Transfusion  ☐ Hospitalization  ☐ Other** | ☐ Unrelated  ☐ Unlikely  ☐ Possible  ☐ Probable  ☐ Definite | _ _ / _ _ / _ _  or ongoing ☐ | ☐ Recovered/resolved  ☐ Recovered/resolved with sequelae  ☐ Recovering/resolving  ☐ Not recovered/not resolved  ☐ Fatal  ☐ Unknown |
| **Definitions**  Severity – Mild (easily tolerated; no or minimal interference with daily activities); Moderate (low level of inconvenience; greater than minimal interference with daily activities); Severe (interrupts normal daily activities; usually incapacitating); Life-threatening (life-threatening consequences; urgent intervention indicated); Fatal (death) | | | | | | |

**SYMPTOM REPORTING FORM - Page 2**

| **Type of AE**  **(one per row only)** | **Onset Date** | **Severity Grade**  **(check one)** | **Actions Taken?**  **(specify below if needed)** | **Is AE related to PQ?**  **(check one)** | **Date Resolved** | **Outcome of AE (check one)** |
| --- | --- | --- | --- | --- | --- | --- |
| ☐Rash  ☐Nausea  ☐Vomiting  ☐Abdominal pain  ☐Dark Urine  Hillmen index: _ _  ☐Diarrhea  ☐Poor appetite  ☐Other (describe): _________________ | _ _ / _ _ / _ _ | ☐ Mild  ☐ Moderate  ☐Severe  ☐ Life-threatening | ☐ None  ☐ Stopped PQ  ☐ Prescribed drug  ☐ Blood Transfusion  ☐ Hospitalization  ☐ Other** | ☐ Unrelated  ☐ Unlikely  ☐ Possible  ☐ Probable  ☐ Definite | _ _ / _ _ / _ _  or ongoing ☐ | ☐ Recovered/resolved  ☐ Recovered/resolved with sequelae  ☐ Recovering/resolving  ☐ Not recovered/not resolved  ☐ Fatal  ☐ Unknown |
| ☐Rash  ☐Nausea  ☐Vomiting  ☐Abdominal pain  ☐Dark Urine  Hillmen index: _ _  ☐Diarrhea  ☐Poor appetite  ☐Other (describe): _________________ | _ _ / _ _ / _ _ | ☐ Mild  ☐ Moderate  ☐Severe  ☐ Life-threatening | ☐ None  ☐ Stopped PQ  ☐ Prescribed drug  ☐ Blood Transfusion  ☐ Hospitalization  ☐ Other** | ☐ Unrelated  ☐ Unlikely  ☐ Possible  ☐ Probable  ☐ Definite | _ _ / _ _ / _ _  or ongoing ☐ | ☐ Recovered/resolved  ☐ Recovered/resolved with sequelae  ☐ Recovering/resolving  ☐ Not recovered/not resolved  ☐ Fatal  ☐ Unknown |
| **Definitions**  Severity – Mild (easily tolerated; no or minimal interference with daily activities); Moderate (low level of inconvenience; greater than minimal interference with daily activities); Severe (interrupts normal daily activities; usually incapacitating); Life-threatening (life-threatening consequences; urgent intervention indicated); Fatal (death) | | | | | | |

**SYMPTOM REPORTING FORM - Page 3**

| **Type of AE**  **(one per row only)** | **Onset Date** | **Severity Grade**  **(check one)** | **Actions Taken?**  **(specify below if needed)** | **Is AE related to PQ?**  **(check one)** | **Date Resolved** | **Outcome of AE (check one)** |
| --- | --- | --- | --- | --- | --- | --- |
| ☐Rash  ☐Nausea  ☐Vomiting  ☐Abdominal pain  ☐Dark Urine  Hillmen index: _ _  ☐Diarrhea  ☐Poor appetite  ☐Other (describe): _________________ | _ _ / _ _ / _ _ | ☐ Mild  ☐ Moderate  ☐Severe  ☐ Life-threatening | ☐ None  ☐ Stopped PQ  ☐ Prescribed drug  ☐ Blood Transfusion  ☐ Hospitalization  ☐ Other** | ☐ Unrelated  ☐ Unlikely  ☐ Possible  ☐ Probable  ☐ Definite | _ _ / _ _ / _ _  or ongoing ☐ | ☐ Recovered/resolved  ☐ Recovered/resolved with sequelae  ☐ Recovering/resolving  ☐ Not recovered/not resolved  ☐ Fatal  ☐ Unknown |
| ☐Rash  ☐Nausea  ☐Vomiting  ☐Abdominal pain  ☐Dark Urine  Hillmen index: _ _  ☐Diarrhea  ☐Poor appetite  ☐Other (describe): _________________ | _ _ / _ _ / _ _ | ☐ Mild  ☐ Moderate  ☐Severe  ☐ Life-threatening | ☐ None  ☐ Stopped PQ  ☐ Prescribed drug  ☐ Blood Transfusion  ☐ Hospitalization  ☐ Other** | ☐ Unrelated  ☐ Unlikely  ☐ Possible  ☐ Probable  ☐ Definite | _ _ / _ _ / _ _  or ongoing ☐ | ☐ Recovered/resolved  ☐ Recovered/resolved with sequelae  ☐ Recovering/resolving  ☐ Not recovered/not resolved  ☐ Fatal  ☐ Unknown |
| **Definitions**  Severity – Mild (easily tolerated; no or minimal interference with daily activities); Moderate (low level of inconvenience; greater than minimal interference with daily activities); Severe (interrupts normal daily activities; usually incapacitating); Life-threatening (life-threatening consequences; urgent intervention indicated); Fatal (death) | | | | | | |

**SYMPTOM REPORTING FORM - Page 4**

| **Type of AE**  **(one per row only)** | **Onset Date** | **Severity Grade**  **(check one)** | **Actions Taken?**  **(specify below if needed)** | **Is AE related to PQ?**  **(check one)** | **Date Resolved** | **Outcome of AE (check one)** |
| --- | --- | --- | --- | --- | --- | --- |
| ☐Rash  ☐Nausea  ☐Vomiting  ☐Abdominal pain  ☐Dark Urine  Hillmen index: _ _  ☐Diarrhea  ☐Poor appetite  ☐Other (describe): _________________ | _ _ / _ _ / _ _ | ☐ Mild  ☐ Moderate  ☐Severe  ☐ Life-threatening | ☐ None  ☐ Stopped PQ  ☐ Prescribed drug  ☐ Blood Transfusion  ☐ Hospitalization  ☐ Other** | ☐ Unrelated  ☐ Unlikely  ☐ Possible  ☐ Probable  ☐ Definite | _ _ / _ _ / _ _  or ongoing ☐ | ☐ Recovered/resolved  ☐ Recovered/resolved with sequelae  ☐ Recovering/resolving  ☐ Not recovered/not resolved  ☐ Fatal  ☐ Unknown |
| ☐Rash  ☐Nausea  ☐Vomiting  ☐Abdominal pain  ☐Dark Urine  Hillmen index: _ _  ☐Diarrhea  ☐Poor appetite  ☐Other (describe): _________________ | _ _ / _ _ / _ _ | ☐ Mild  ☐ Moderate  ☐Severe  ☐ Life-threatening | ☐ None  ☐ Stopped PQ  ☐ Prescribed drug  ☐ Blood Transfusion  ☐ Hospitalization  ☐ Other** | ☐ Unrelated  ☐ Unlikely  ☐ Possible  ☐ Probable  ☐ Definite | _ _ / _ _ / _ _  or ongoing ☐ | ☐ Recovered/resolved  ☐ Recovered/resolved with sequelae  ☐ Recovering/resolving  ☐ Not recovered/not resolved  ☐ Fatal  ☐ Unknown |
| **Definitions**  Severity – Mild (easily tolerated; no or minimal interference with daily activities); Moderate (low level of inconvenience; greater than minimal interference with daily activities); Severe (interrupts normal daily activities; usually incapacitating); Life-threatening (life-threatening consequences; urgent intervention indicated); Fatal (death) | | | | | | |

**SYMPTOM REPORTING FORM - Page 5**

| **Type of AE**  **(one per row only)** | **Onset Date** | **Severity Grade**  **(check one)** | **Actions Taken?**  **(specify below if needed)** | **Is AE related to PQ?**  **(check one)** | **Date Resolved** | **Outcome of AE (check one)** |
| --- | --- | --- | --- | --- | --- | --- |
| ☐Rash  ☐Nausea  ☐Vomiting  ☐Abdominal pain  ☐Dark Urine  Hillmen index: _ _  ☐Diarrhea  ☐Poor appetite  ☐Other (describe): _________________ | _ _ / _ _ / _ _ | ☐ Mild  ☐ Moderate  ☐Severe  ☐ Life-threatening | ☐ None  ☐ Stopped PQ  ☐ Prescribed drug  ☐ Blood Transfusion  ☐ Hospitalization  ☐ Other** | ☐ Unrelated  ☐ Unlikely  ☐ Possible  ☐ Probable  ☐ Definite | _ _ / _ _ / _ _  or ongoing ☐ | ☐ Recovered/resolved  ☐ Recovered/resolved with sequelae  ☐ Recovering/resolving  ☐ Not recovered/not resolved  ☐ Fatal  ☐ Unknown |
| ☐Rash  ☐Nausea  ☐Vomiting  ☐Abdominal pain  ☐Dark Urine  Hillmen index: _ _  ☐Diarrhea  ☐Poor appetite  ☐Other (describe): _________________ | _ _ / _ _ / _ _ | ☐ Mild  ☐ Moderate  ☐Severe  ☐ Life-threatening | ☐ None  ☐ Stopped PQ  ☐ Prescribed drug  ☐ Blood Transfusion  ☐ Hospitalization  ☐ Other** | ☐ Unrelated  ☐ Unlikely  ☐ Possible  ☐ Probable  ☐ Definite | _ _ / _ _ / _ _  or ongoing ☐ | ☐ Recovered/resolved  ☐ Recovered/resolved with sequelae  ☐ Recovering/resolving  ☐ Not recovered/not resolved  ☐ Fatal  ☐ Unknown |
| **Definitions**  Severity – Mild (easily tolerated; no or minimal interference with daily activities); Moderate (low level of inconvenience; greater than minimal interference with daily activities); Severe (interrupts normal daily activities; usually incapacitating); Life-threatening (life-threatening consequences; urgent intervention indicated); Fatal (death)  ****Other information (actions taken): ___________________________________________________________________________________**  **___________________________________________________________________________________________________________________** | | | | | | |

**Concomitant medication Table Page 1 (only if any symptoms with grading 3 or 4 occurred)**

| **Name of Drug**  **(please use a new row for each drug)** | **Dose** | **Unit** | **Freq (number of times per day)** | **Route** | **Date Started (dd/mm/yy)** | **Date Stopped (dd/mm/yy)**  **Or Continuing?** | **Indication**  **(please make sure that this is in accordance with the symptoms table)** |
| --- | --- | --- | --- | --- | --- | --- | --- |
|  |  | ☐ mg  ☐ g  ☐ ml  ☐ mcg  ☐ drops  ☐tsp  ☐tablet/capsule  ☐don’t know  ☐ other:_____ |  | ☐ oral  ☐ topical  ☐ IM  ☐ rectal  ☐ IV  ☐ don’t know  ☐ other : ________ | _ _ / _ _ / _ _ | _ _ / _ _ / _ _  ☐Continuing |  |
|  |  | ☐ mg  ☐ g  ☐ ml  ☐ mcg  ☐ drops  ☐tsp  ☐tablet/capsule  ☐don’t know  ☐ other:_____ |  | ☐ oral  ☐ topical  ☐ IM  ☐ rectal  ☐ IV  ☐ don’t know  ☐ other : ________ | _ _ / _ _ / _ _ | _ _ / _ _ / _ _  ☐Continuing |  |
|  |  | ☐ mg  ☐ g  ☐ ml  ☐ mcg  ☐ drops  ☐tsp  ☐tablet/capsule  ☐don’t know  ☐ other:_____ |  | ☐ oral  ☐ topical  ☐ IM  ☐ rectal  ☐ IV  ☐ don’t know  ☐ other : ________ | _ _ / _ _ / _ _ | _ _ / _ _ / _ _  ☐Continuing |  |

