## Concomitant treatment

Patients under regular medication at trial entry for conditions other than malaria, will have this documented on the CRF and will be asked to continue medication as usual. Any additional medications taken within the follow-up period must be documented in the CRF. Patients who prematurely discontinue trial medication, or who fail to respond to trial medication and receive other anti-malarial therapy will have this documented. Drugs with antimalarial activity should be avoided (Annex I).

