**Concomitant medication Table Page 2 (only if any symptoms with grading 3 or 4 occurred)**

| **Name of Drug**  **(please use a new row for each drug)** | **Dose** | **Unit** | **Freq (number of times per day)** | **Route** | **Date Started (dd/mm/yy)** | **Date Stopped (dd/mm/yy)**  **Or Continuing?** | **Indication**  **(please make sure that this is in accordance with the symptoms table)** |
| --- | --- | --- | --- | --- | --- | --- | --- |
|  |  | ☐ mg  ☐ g  ☐ ml  ☐ mcg  ☐ drops  ☐tsp  ☐tablet/capsule  ☐don’t know  ☐ other:_____ |  | ☐ oral  ☐ topical  ☐ IM  ☐ rectal  ☐ IV  ☐ don’t know  ☐ other : ________ | _ _ / _ _ / _ _ | _ _ / _ _ / _ _  ☐Continuing |  |
|  |  | ☐ mg  ☐ g  ☐ ml  ☐ mcg  ☐ drops  ☐tsp  ☐tablet/capsule  ☐don’t know  ☐ other:_____ |  | ☐ oral  ☐ topical  ☐ IM  ☐ rectal  ☐ IV  ☐ don’t know  ☐ other : ________ | _ _ / _ _ / _ _ | _ _ / _ _ / _ _  ☐Continuing |  |
|  |  | ☐ mg  ☐ g  ☐ ml  ☐ mcg  ☐ drops  ☐tsp  ☐tablet/capsule  ☐don’t know  ☐ other:_____ |  | ☐ oral  ☐ topical  ☐ IM  ☐ rectal  ☐ IV  ☐ don’t know  ☐ other : ________ | _ _ / _ _ / _ _ | _ _ / _ _ / _ _  ☐Continuing |  |

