**Concomitant medication Table Page 3 (only if any symptoms with grading 3 or 4 occurred)**

| **Name of Drug**  **(please use a new row for each drug)** | **Dose** | **Unit** | **Freq (number of times per day)** | **Route** | **Date Started (dd/mm/yy)** | **Date Stopped (dd/mm/yy)**  **Or Continuing?** | **Indication**  **(please make sure that this is in accordance with the symptoms table)** |
| --- | --- | --- | --- | --- | --- | --- | --- |
|  |  | ☐ mg  ☐ g  ☐ ml  ☐ mcg  ☐ drops  ☐tsp  ☐tablet/capsule  ☐don’t know  ☐ other:_____ |  | ☐ oral  ☐ topical  ☐ IM  ☐ rectal  ☐ IV  ☐ don’t know  ☐ other : ________ | _ _ / _ _ / _ _ | _ _ / _ _ / _ _  ☐Continuing |  |
|  |  | ☐ mg  ☐ g  ☐ ml  ☐ mcg  ☐ drops  ☐tsp  ☐tablet/capsule  ☐don’t know  ☐ other:_____ |  | ☐ oral  ☐ topical  ☐ IM  ☐ rectal  ☐ IV  ☐ don’t know  ☐ other : ________ | _ _ / _ _ / _ _ | _ _ / _ _ / _ _  ☐Continuing |  |
|  |  | ☐ mg  ☐ g  ☐ ml  ☐ mcg  ☐ drops  ☐tsp  ☐tablet/capsule  ☐don’t know  ☐ other:_____ |  | ☐ oral  ☐ topical  ☐ IM  ☐ rectal  ☐ IV  ☐ don’t know  ☐ other : ________ | _ _ / _ _ / _ _ | _ _ / _ _ / _ _  ☐Continuing |  |

**Did the patient take any traditional medicines along with PQ at the time of treatment or in the two-week period prior to the onset of the event?**

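### The case record form asks for other drugs only after a grade 3 or 4 symptom, although the protocol text requires them to be documented for every patient

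*Protocol*

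**What the plan says.** The Concomitant treatment section (4.4.2 in the contents list) sets recording duties that do not depend on how the patient fares. For medication at entry: "Patients under regular medication at trial entry for conditions other than malaria, will have this documented on the CRF". For follow-up: "Any additional medications taken within the follow-up period must be documented in the CRF". Other antimalarial therapy after failure or early discontinuation is also to be documented. The section adds: "Drugs with antimalarial activity should be avoided (Annex I"). Annex I then lists the agents, among them several antibiotics and sulfa drugs.

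Annex IX holds the case record form. Its drug table has three pages, headed "Concomitant medication Table Page 1 (only if any symptoms with grading 3 or 4 occurred"), "Concomitant medication Table Page 2 (only if any symptoms with grading 3 or 4 occurred") and "Concomitant medication Table Page 3 (only if any symptoms with grading 3 or 4 occurred"). The table asks for drug name, dose, unit, frequency, route and dates. Its indication column carries the instruction "please make sure that this is in accordance with the symptoms table". After the third page comes a separate item that begins "Did the patient take any traditional medicines along with PQ at the time of treatment".

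**The concern.** The protocol text and the form that implements it give opposite instructions, and site staff will follow the form in front of them. The restriction stands on all three pages, so it is unlikely to be a slip on one of them.

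Three uses of the data are at stake:

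- **Relatedness.** The primary objective is side effects after primaquine. The symptom form asks for every adverse event, whatever its grade, whether it is related to primaquine. That judgement needs to know what else the patient took.
- **Efficacy.** Parasitaemia on days 1 to 3 and recurrence within 30 days can be affected by an Annex I drug. Whether such drugs were avoided can be verified only if drugs are recorded for all patients.
- **Reading of blanks.** When a page is opened only for some patients, an empty page elsewhere does not separate no drug taken from not asked.

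**Working it through.** No figure in the protocol depends on this point, so the check sets the text against the form.

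1. **The duty.** Section 4.4.2 covers regular medication at entry and all additional medication in follow-up. It sets no threshold of symptom or severity.

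2. **The trigger on the form.** The three drug pages open only on a symptom of grading 3 or 4. The symptom reporting form grades in words: mild, moderate, severe, life-threatening. Taken in order, 3 is severe and 4 is life-threatening. This mapping is natural, but it is inferred and not printed.

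3. **Other places where a drug could be written.**

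| Part of Annex IX | What it records | Does it identify another drug? |
| --- | --- | --- |
| Visit pages, day 0 to day 30 | AL, CQ and PQ | No field for other drugs |
| Unscheduled visit pages | Temperature, slide, haemoglobin, methaemoglobin | No treatment field |
| Symptom form, actions taken | Tick box for a prescribed drug, any grade | No name, dose or date in the box |
| Symptom form, foot of page 5 | Free-text lines on actions taken | Can name a drug given for a reported event |
| Traditional medicine item | Yes/no and details | Traditional medicines only |
| End of study form | Rescue before PQ as a reason for stopping | Partial; nothing comparable after PQ has started |

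4. **What this leaves.** A patient with no symptom, or with only mild or moderate ones, has no structured record of other drugs on the pages shown. The tick box and free text concern what was done about a reported event. They do not ask about entry medication, or about a drug bought for another reason. The indication instruction pulls the table the same way, towards drugs given for a listed symptom.

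5. **Haemoglobin endpoints.** The safety endpoints include haemoglobin below 7 g/dl and a drop of more than 25%. Both are measured values, and the table's trigger is a symptom. A patient can meet either endpoint without a severe symptom, and nothing in the form then requires the drug table to be filled in.

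6. **Number of patients.** The Sample Size section proposes about 50 vivax and 160 falciparum cases, 50 + 160 = 210. The table stays closed for all of them who have no severe or life-threatening symptom. The documents give neither the expected share with such a symptom nor the share taking other drugs, so no count follows.

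**The case against.** Several points on the other side have force.

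- **The public form may be incomplete.** Study Procedures says that the questionnaire collects drug hypersensitivity, and the schedule includes a pregnancy test. Neither appears in the form shown. A day 0 medication item may have been on a removed page. This stands, and for that reason the point rests on the three headings and not on the absence of a field elsewhere.
- **Some drugs are captured.** A reader might infer that drug exposure is seen only in patients with bad outcomes. That is too broad. AL, CQ and PQ are recorded for everyone. A drug prescribed for a mild event can be ticked and named in the free text. The Rescue treatment section says that quinine for treatment failure is noted on the form.
- **A haemoglobin fall might still open the table.** It could be entered under the symptom form's category for other events and graded severe. The form allows this but does not require it.
- **The traditional medicine item** is separate from the table, and the first part of the question needs no event. It should not be counted as restricted.
- **No biased comparison is planned.** A reader might infer that associations between drug use and side effects will be inflated, because exposure is recorded conditional on severity. The Statistical analyses section contains no such comparison; its relative risk is by G6PD category. The inference would matter only if someone later ran that analysis.

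None of this reconciles the headings with section 4.4.2.

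**Conclusion.** The contradiction is certain from the text: an unconditional duty in section 4.4.2, and a restriction to grade 3 or 4 symptoms on every page of the drug table. If the form is followed as printed, names, doses and dates of other drugs are collected systematically only in patients with severe or life-threatening symptoms. The relatedness of milder events, and of haemoglobin falls without a severe symptom, cannot then be checked against other drugs. Annex I use that bears on parasitaemia and recurrence may go undetected.

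The conclusion assumes that staff follow the headings, and that grading 3 or 4 means severe or life-threatening. It does not say that other drugs are never recorded, that any planned estimate is biased in a known direction, or how many patients are affected. The documents support none of those. The defect deserves correction before enrolment, because an analysis plan cannot restore data that were not collected.

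**What to change.** Delete the condition on grade 3 or 4 symptoms from the headings of all three concomitant medication pages. Complete the table for every patient on day 0 and at each scheduled and unscheduled visit, as section 4.4.2 already requires, with an explicit entry when no other drug was taken. When clearance, recurrence and haemoglobin results are reported, flag patients who took an Annex I or other antimalarial drug, with its dates.

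Flagging is preferable to dropping these patients. Drug use after baseline may itself follow persistent illness, so excluding on it can introduce bias, and a drug started late in follow-up cannot have affected clearance on days 1 to 3.

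The cost is a change of form wording and a few minutes of recording per patient, with no new procedure. The Sample Size section says that primary-objective results will be pooled with studies using similar tools, so the change may need to be agreed with the other sites.
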